We present the protocol for a cluster-randomized controlled trial of a supply-side CHW delivered health, nutrition, and responsive stimulation intervention alone and in combination with a demand-side CCT intervention to promote antenatal care and routine child growth monitoring visit attendance in rural Tanzania. The co-primary outcomes of the trial are child development and linear growth. We will also examine a range of secondary maternal, child, and household outcomes. This trial is intended to inform whether policymakers in Tanzania and similar settings should consider adding a responsive stimulation to CHW curriculums and whether coordination of CHW and CCT programs can improve child growth and development.

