### Sample size

Sample size calculations were based on randomization of 12 clusters with a cluster size of approximately 50 mother/caregiver-child pairs. We assumed a nominal Type I error rate (alpha) of 0.05 and assume a coefficient of variation of 0.49 an intra-cluster correlations of 0.01. We will have 80% power to detect a standardized mean difference (SMD) of 0.40 standard deviations in normalized anthropometric outcomes (HAZ, WHZ, WAZ), and 0.53 standard deviations of development z-scores. These are quite large effect sizes; however, this is a proof-of-concept trial and there is potential of the intervention package and the combination of CHWs and CCT to provide a sizable impact on child growth and development.

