### Randomization and interventions

Village clusters will be allocated in a 1:1:1 ratio to one of the three trials arms: (i) CHW, (ii) CHW + CCT, or (iii) Control. Stratified randomization will be done by a non-study statistician in Boston, USA according to a computer-generated randomization list with sequence blocks of three. Randomization will be stratified by semi-urban (six villages) and rural (six villages) villages to increase the likelihood of baseline balance.

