### Statistical analyses

All primary analyses will be conducted based on the intention-to-treat (ITT) principle. Women who moved to neighboring villages will be analyzed in the village originally randomized. Despite randomization, it is possible that there may be some degree of imbalance of baseline prognostic factors between randomized trials arms due to the small number of clusters. As a result, we will re-assess intervention effects after adjusting for factors that are potentially imbalanced between randomized trial arms. All analyses will account for village clustering. We will use linear regression models to assess the intervention effect on individual-level BSID-III domain scores, HAZ, and other secondary continuous outcomes. We will use log-binomial models to assess treatment effects on binomial outcomes. Linear mixed effects models and generalized linear mixed models will be used to assess longitudinal continuous and binomial outcomes, respectively. We will also examine effect modification of any treatment effect by predefined baseline variables: maternal age, maternal education, maternal/caregiver parenting knowledge, parity, household wealth, marital status, paternal residence in household, maternal depression, maternal social support, child age, child sex, number of CHW visits received, and number of CCTs received. We will also present analyses collapsing the CHW and CHW + CCT arms.

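### Collapsing the CHW and CHW + CCT arms counts any sizeable CCT effect as between-village error; an equal-weight contrast from the three-arm model avoids this for one degree of freedom

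*Protocol article*

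**What the plan says.** In the protocol article, the last sentence of Statistical analyses reads "We will also present analyses collapsing the CHW and CHW + CCT arms". The same section says that clustering by village is handled in every analysis and that continuous outcomes are modelled by linear regression on individual data. It gives no separate model for the collapsed comparison.

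The design inputs are in Sample size and in Randomization and interventions: "randomization of 12 clusters with a cluster size of approximately 50 mother/caregiver-child pairs"; "Village clusters will be allocated in a 1:1:1 ratio to one of the three trials arms"; "We assumed a nominal Type I error rate (alpha) of 0.05"; "assume a coefficient of variation of 0.49 an intra-cluster correlations of 0.01". Each arm therefore has four villages, and the collapsed comparison sets eight against four.

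The Background names as one of the trial's two policy questions "whether coordination of CHW and CCT programs can improve child growth and development".

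**The concern.** Merging two arms under one mean is right only if CCT adds nothing, and the CHW + CCT arm exists to find out whether it does. If CCT has an effect, the systematic gap between the four CHW and the four CHW + CCT villages goes into the residual. There it is treated as random variation between villages, although it is a known, randomized difference.

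The collapsed comparison is the best-powered look at any CHW programme against control that 12 villages allow. Part of that advantage would be lost when CCT adds a sizeable benefit.

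There is a lesser point. If individuals are weighted equally, the mix of the two interventions in the pooled estimate depends on how many dyads each arm happened to enrol, not on the 1:1 allocation of villages.

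**Working it through.** **Inputs.** From the article: 12 villages, 4 per arm, size 50, ICC 0.01, alpha 0.05, CV 0.49. Assumed: two-sided test; CV refers to cluster size (the article does not say); no stratum term in either model; CCT increment delta from 0 to 0.40 SD (the article gives none).

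**The article's own figure.** Sample size states: "We will have 80% power to detect a standardized mean difference (SMD) of 0.40 standard deviations in normalized anthropometric outcomes".
- Design effect = 1 + ((1 + 0.49²) × 50 − 1) × 0.01 = 1.61.
- Standard error, 4 v 4 villages = √(2 × 1.61 / 200) = 0.127.
- With t on 9 df (12 villages − 3 arms), the detectable difference is 0.3997 and power at 0.40 is 80.1%.

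The inputs as read here therefore reproduce the stated 0.40. Other readings give 0.355 (normal), 0.427 (6 df) and 0.395 (10 df).

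**Effect of collapsing.** The variance of a village mean is 1.61 / 50 = 0.0322. The four CHW and four CHW + CCT villages lie delta/2 either side of their common mean. This adds 8 × (delta/2)² = 2 × delta² to the residual sum of squares on 10 df, which is 0.2 × delta² in the mean square. With equal village weights, the contrast ½(CHW − control) + ½(CHW + CCT − control) has the same point estimate, but its error term stays at 0.0322 on 9 df.

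Half-widths, with variance factor 1/8 + 1/4 = 0.375:
- Contrast: 2.262 × √(0.0322 × 0.375) = 0.249 at every delta.
- Collapsed: 2.228 × √((0.0322 + 0.2 × delta²) × 0.375).

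| delta | mean-square ratio | collapsed half-width | ratio to contrast | collapsed coverage |
|---|---|---|---|---|
| 0 | 1.00 | 0.245 | 0.985 | 95.0% |
| 0.10 | 1.06 | 0.252 | 1.015 | 95.6% |
| 0.20 | 1.25 | 0.274 | 1.10 | 96.9% |
| 0.30 | 1.56 | 0.306 | 1.23 | 98.2% |
| 0.40 | 1.99 | 0.346 | 1.39 | 99.2% |

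**Break-even.** The extra df offsets the inflation when 1 + 0.2 × delta² / 0.0322 = (2.262 / 2.228)² = 1.031, so delta is about 0.07.

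**Power**, with an assumed CHW effect of 0.20:
- delta 0.20 (average effect 0.30): 60.6% collapsed, about 68% contrast.
- delta 0.40 (average effect 0.40): 68.2% collapsed, about 90% contrast.

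A simulation with unequal villages (CV 0.49, equal-weight village means) gives half-widths of 0.278 v 0.254 and power of 57% v 64% at delta 0.20. At delta 0.40 it gives 0.348 v 0.255, 65% v 86%, and coverage of 99% v 95%.

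**Higher ICC.** By the same formula, the article's 0.53 SD for development would need an ICC of about 0.03, which it does not state. At that ICC the width ratio is 1.05 (delta 0.20) and 1.23 (delta 0.40).

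**Cluster-robust errors** on individual data (equal villages, t on 11 df). The mean standard error is 0.102 v 0.092 at delta 0.20 and 0.120 v 0.092 at 0.40. Power is 74% v 80% and 63% v 80%. Coverage at delta 0.10 is 92% collapsed and 90% contrast. With unequal villages and a normal critical value, coverage is 87% v 85% at delta 0 and 95% v 86% at 0.40.

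**Enrolment mix.** With gamma village sizes at CV 0.49 and individual weighting, the CHW + CCT share of the merged arm runs from 0.36 to 0.64 (5th to 95th percentile). That moves the target by 0.14 × delta: about 0.06 SD at delta 0.40 and 0.03 SD at 0.20.

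**The case against.** The analysis is announced as an addition. The comparisons that answer the CCT question do not depend on it, and the error is conservative: with a true average effect of zero and delta 0.40, the collapsed test rejects in only 0.8% of trials. The article gives no CCT effect size. Its Background cites a meta-analysis of 17 CCT programmes that found nothing for growth, and 0.40 SD on top of CHW equals the whole pairwise difference that the trial is sized for. The model is also unstated, so a two-group recode is only the natural reading. All of this stands, and it limits the weight of the point.

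A reader might infer more than the documents support:
- **That collapsing loses power whenever CCT works.** It does not below about 0.07 SD, and at 0.10 SD the interval is only 1.5% wider. When CCT adds nothing and the CHW effect is 0.30, collapsing has 69% power against 56% for one pairwise test.
- **That the collapsed interval is always too wide.** This holds for a model-based village error term. With ordinary cluster-robust errors it mostly is not too wide, and the three-arm contrast under-covers more.
- **That the stated 0.40 arises only with 9 df, so pairwise contrasts must come from a 12-village fit.** The article does not define the CV or give attrition. A normal approximation with 35 analysed per village (an assumed 30% loss) also gives 0.400. Nor does the article propose separate two-arm fits.
- **That the result will be taken for the CHW effect.** The article labels it as a merger of both arms.

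**Conclusion.** The point holds as a modest improvement to a supplementary analysis. Under a two-group recode with a model-based village error term, ICC 0.01 and CV 0.49 for cluster size, collapsing costs nothing for a CCT increment below about 0.07 SD. It makes the interval about 10% wider at an assumed 0.20 SD and about 35–40% wider at an assumed 0.40 SD, with about 7 and 20 points of power lost. At ICC 0.03 the widening is about 5% and just under 25%. Neither the three-arm comparisons nor the false-positive rate is put at risk. The size rests on a CCT increment that the documents do not give. Grade: consider.

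**What to change.** Replace the sentence on collapsing with wording such as: *From the three-arm model fitted to all 12 villages, we will also estimate the average intervention effect, ½(CHW − control) + ½(CHW + CCT − control), with a small-sample method for 12 clusters (for example t on 9 df with a village-level or mixed-model error term, or bias-corrected robust errors). This is not an estimate of the CHW-only effect.*

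The small-sample clause is needed, because with uncorrected robust errors the contrast covers only about 85–90%. The fixed half-and-half weights also remove the dependence on enrolment. The cost is one sentence and one error degree of freedom (9 instead of 10), so the interval is about 1–2% wider if CCT has no effect.

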### Ethics

The trial protocol was approved by the Ifakara Health Institute IRB (reference number 007–2017), the Tanzanian National Health Research Ethics Sub-Committee (NatHREC; reference no. NIMR/HQ/R.8a/Vol.IX/2538), and the Harvard T.H. Chan School of Public Health Institutional Review Board (reference no. IRB17–1001). Written informed consent will be sought from mothers and caregivers. The trial results will be disseminated locally in Tanzania and in international academic journals.

### Trial status

Trial enrollment started on 14 September 2017 and follow-up is ongoing as of 16 May 2019.

## Discussion

Sustainable Development Goal 4.2 calls for all countries to ensure that all girls and boys have access to quality early childhood development, care and pre-primary education by 2030 [29]. In order to address this call, we designed the current trial to examine the effect of a supply-side CHW interventions alone and in combination with a demand-side CCT intervention. These interventions were selected as Tanzania is currently in the process of implementing a national cadre of CHWs and CCTs have shown promise in the context of Latin America [14, 15]. The primary outcomes of the trial will be child development and child linear growth and we have included a range of maternal, child, and household secondary outcomes. This trial will contribute to the growing literature on integration of child health, nutrition, and responsive stimulation and social protection programs, particularly in the context of sub-Saharan Africa where the evidence is sparse.

There are a few limitations to the trial. As a proof-of-concept trial we will not have statistical power to detect small effect sizes on the primary or secondary outcomes of interest. Nevertheless, the comprehensive and integrated intervention package may provide large benefits. Second, we will only follow-up children for 18 months and as a result we cannot make conclusions about the long-term effects of CHWs and CCT interventions. Third, while the CCTs are designed to encourage clinic attendance, we did not provide quality improvement for clinic services and child growth monitoring. As a result, we may underestimate the potential effect of the CCTs.

This cluster randomized controlled trial will provide evidence whether CHW and CCT programs can be integrated to support child growth and development in rural Tanzania. The trial will also inform whether larger implementation evaluations should be pursued. The results of the trial are likely generalizable to similar rural contexts in sub-Saharan Africa that face a high burden of linear growth faltering and suboptimal child development.

## Data Availability

The datasets generated from the current study are available from the corresponding author.

## Abbreviations

BSID-III: Bayley Scales of Infant Development III
CCT: Conditional cash transfer
CHW: Community health worker
CKCDI: Caregiver Knowledge of Child Development Inventory
HAZ: Height-for-age z-score
HCAZ: Head circumference-for-age z-score
HDSS: Health and Demographic Surveillance
HSCL-25: Hopkins Symptom Checklist
IMCI: Integrated Management of Childhood Illness
LMIC: Low and middle-income countries
MUAC: Mid-upper arm circumference
SMD: Standardized mean difference
WAZ: Weight-for-age z-score
WEAI: Women’s Empowerment in Agriculture Index
WHZ: Weight-for-height z-score
